### Study setting and population

The study will recruit centres worldwide through pre-existing research networks and collaboratives, developed through the National Institute for Health and Care Research Global Health Research Groups on Neurotrauma and Acquired Brain and Spine Injury. Invitation to participate will also be extended through relevant professional societies and academic groups.

Any hospital admitting patients with sICH worldwide is eligible to participate. A minimum of one case must be submitted by each site during the 30-day chosen study period. At each site, the local team will comprise a local lead, up to two additional data collectors, a data validator and supervising clinician. The study recruitment is planned to run for a total of 12 months (February 2025–January 2026). Eligible patients presenting with sICH over a consecutive 30-day period chosen by each individual recruiting centre during the overall study period will be enrolled. Patients will be followed up until 30 days, death or discharge from hospital, whichever comes first. All data will be submitted to the central study team for inclusion in the final dataset. A minimum sample size of 712 patients will be recruited, as detailed in the Statistical Analysis section below.

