### Statistical analysis

A formal a priori statistical plan will be produced for data analysis. In short, the primary analysis will comprise statistical descriptive analysis of patient-level variables and the characterisation of processes of care using descriptions of provider profiling data and patient-level process variables.

Country groups will be defined using the human development index (HDI), a recognised index of human development.^21^ The 30-day mortality will be reported for each HDI tier. Further analyses will stratify against other indices of economic development and health. Multivariable logistic regression models will be used to investigate the primary and secondary outcomes. Provider profile summaries will be compared with current evidence-based best practices to identify gaps and associations with care processes and case mix.

There is limited robust epidemiological data on sICH globally across income settings, with mortality rates for hospital cohorts reported between 20% and 33% in HICs and 39% and 62% in LMICs.^22^,^28^ Therefore, an accurate sample size calculation is not feasible. However, taking conservative mortality estimates indicating a 30-day mortality rate for sICH of around 30% in HICs and up to 40% in LMICs, using an alpha value of 0.05 and power of 80% to show a 10% difference between HIC and LMIC settings, a total of 712 patients would need to be recruited. Subgroup analyses will be performed, for example, to describe differences between sICH subtypes or hospital type.

Based on the data and experience from other observational studies with a similar methodology, we would expect that each centre enrols around three to five patients over a 30-day study period.^19^ Therefore, with around 150 recruiting centres from our pre-existing research network, we would expect to meet and exceed the sample size required. Given the nature of this international study, missing values are expected and could affect some participating centres more than others. Patients with at least 70% data field completeness will be included in the analysis. At each site, a data validator, independent from the primary data collectors, will validate accuracy for key study variables to ensure completeness and data accuracy.

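### The stated recruitment inputs (about 150 centres, 3 to 5 patients each) give 450 to 750 patients and do not support the expectation of meeting and exceeding 712

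*Protocol article*

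**What the plan says.** All the relevant statements are in the protocol article.

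- **Required size** (Statistical analysis): "a total of 712 patients would need to be recruited". It assumes a "30-day mortality rate for sICH of around 30% in HICs and up to 40% in LMICs". The error rate is set at alpha 0.05, and the 10-point gap between the two settings is to be detected with 80% power.
- **Yield per centre** (Statistical analysis): "we would expect that each centre enrols around three to five patients over a 30-day study period".
- **Inference** (Statistical analysis, the next sentence, introduced as following from the yield): "with around 150 recruiting centres from our pre-existing research network, we would expect to meet and exceed the sample size required".
- **Recruitment window** (Study setting and population): eligible patients presenting "over a consecutive 30-day period chosen by each individual recruiting centre during the overall study period will be enrolled". This is one window per centre, and a site qualifies with a single case.
- **Status of 712** (Study setting and population): "A minimum sample size of 712 patients will be recruited, as detailed in the Statistical Analysis section below". The Abstract describes 712 as a target instead.
- **Exclusions** (Eligibility criteria; Statistical analysis): patients whose records fall short of about 70% of data fields are left out of the analysis, and some missing data are anticipated.

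**The concern.** The article prints two inputs and a conclusion drawn from them, and the conclusion does not follow. Multiplying the number of centres by the yield per centre gives a range that lies mostly below 712. Only the upper end reaches it, and then by a small margin that exclusions could remove.

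The recruitment sentence is the article's evidence that 712 is feasible, and 712 is the only size to which the comparison of mortality between high-income (HIC) and low- and middle-income (LMIC) settings is tied. A team relying on the sentence could stop seeking centres at about 150 in the belief that there is a margin, when the stated figures show little or none.

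**Working it through.** **Step 1. Reproduce 712.** Inputs from Statistical analysis: p₁ = 0.30, p₂ = 0.40, alpha 0.05, power 80%. The article does not state sidedness or group ratio; a two-sided test and equal groups are assumed. With p̄ = 0.35 and pooled variance under the null, the number per group is

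n = [1.96·√(2·0.35·0.65) + 0.8416·√(0.30·0.70 + 0.40·0.60)]² / 0.10²

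= [1.96·√0.455 + 0.8416·√0.45]² / 0.01

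= (1.3221 + 0.5646)² / 0.01 ≈ 355.9, rounded up to 356.

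The total is 2 × 356 = **712**, an exact match. The two assumptions are therefore reasonable, and the required size is not in question.

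**Step 2. Projected yield.** Yield = centres × patients per centre, with one window per centre.

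| Patients per centre | Yield from 150 centres | Difference from 712 |
|---|---|---|
| 3 | 450 | −262 (−37%) |
| 4 | 600 | −112 (−16%) |
| 5 | 750 | +38 (+5%) |

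Mean yield needed with 150 centres: 712 / 150 = 4.75 per centre.

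**Step 3. Centres needed for 712.**

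- At 5 per centre: 712 / 5 = 142.4, so 143 centres.
- At 4 per centre: 712 / 4 = 178 centres.
- At 3 per centre: 712 / 3 = 237.3, so 238 centres.

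**Step 4. Margin for exclusions.** At the best case of 750, the loss that brings the analysed number down to 712 is 1 − 712/750 = 5.1%. The article states no expected loss, so this is a break-even point and not a forecast. As a purely illustrative assumption, losses of 5% and 10% would leave 712.5 and 675 of the 750.

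**Step 5. Power at each yield**, for 30% versus 40%, two-sided 0.05, equal groups, independent patients, with N the total:

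Power = Φ{ [0.10·√(N/2) − 1.96·√0.455] / √0.45 }

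- N = 450: Φ(0.265) = 60.5% (0.6046)
- N = 600: Φ(0.611) = 72.9%
- N = 712: 80.0%
- N = 750: Φ(0.916) = 82.0%

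Steps 2 to 4 do not depend on the assumptions about sidedness, group ratio or independence. Only Step 5 does.

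**The case against.** The strongest reply is that 150 is not a cap. The article ties 150 to the existing network, but Study setting and population also extends invitations through professional societies and academic groups, and the Abstract adds conferences and courses and opens participation to any centre worldwide. Recruitment runs for 12 months. This stands: a reader might infer that the study will probably end short, and the documents do not support that. It does not rescue the sentence, because no number is given for outside centres and the expectation is expressly rested on the 150.

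Both inputs are approximate, and the article gives no mean yield. That also stands: 600 is only the arithmetic midpoint, not a figure the article expects, and nothing says that each value between 3 and 5 is equally likely. A pilot is mentioned without results. Still, at 4 per centre the gap is 28 centres (178 − 150), which is more than the looseness of an approximate figure.

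A reader might also infer that the stated 80% power is wrong. It is not. It is conditional on 712 patients, and 712 reproduces exactly.

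Finally, the practical loss may be smaller than Step 5 suggests. The article calls its mortality assumptions conservative, cites hospital mortality of 20–33% in HICs and 39–62% in LMICs, says that an accurate calculation is not feasible, and describes the primary analysis as descriptive. With 30% versus 45%, the same method gives about 91% power at 450 patients. This tempers the consequence. It leaves the mismatch between the stated inputs and the stated conclusion untouched.

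**Conclusion.** The feasibility statement is wrong as written. Around 150 centres at around three to five patients each yield 450 to 750 patients. They reach 712 only if the mean is about 4.75 or more per centre, and the surplus is at most 38 patients before exclusions. An exclusion rate above about 5% would remove even that surplus, although the article gives no rate.

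The required size of 712 is sound for its inputs. Whether the study will reach it cannot be settled from the article, because recruitment is open beyond the network. The matching power of about 60% to 82% rests on a 30% versus 40% difference, a two-sided 0.05 test, equal groups and independent patients; the last three are assumptions that the article does not state.

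This should be fixed, but it is not critical: no analysis, eligibility rule or data item changes.

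**What to change.** In Statistical analysis, replace the sentence on meeting and exceeding the sample size with:

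> About 150 network centres at 3–5 patients each would give 450–750 patients before exclusions, i.e. about 60% to 82% power for 30% vs 40% mortality (two-sided 0.05, equal groups, independent patients; 73% at 600). Reaching 712 needs about 143 centres at 5 patients each, 178 at 4 or 238 at 3, so centres beyond the existing network are being sought.

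Alternatively, keep the expectation and justify a mean of at least 4.75 patients per centre, for example from the pilot if its data support that.

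In Study setting and population, where the article now says "A minimum sample size of 712 patients will be recruited", describe 712 as a target, in line with the Abstract.

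The cost is wording only. The downside is a less favourable stated expectation; the gain is an explicit number of centres to seek.

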### Limitations

There are limitations worth noting in this study. First, long-term follow-up data are not feasible for this study design. Additionally, this pragmatic study will only include patients reaching hospital for their sICH and, therefore, cannot provide comprehensive data on population-level sICH disease burden. Data validation will ensure robustness of the dataset; however, some missing data are expected in this collaborative study. Finally, this study will not test the efficacy of specific management strategies or novel interventions for patients with sICH.

### Ethics and dissemination

The study received ethical approval from the University of Cambridge Psychology Research Ethics Committee (PRE.2024.070). Using the UK NHS Health Research Authority tool (https://www.hra-decisiontools.org.uk/research/),^29^ this study is considered locally as a clinical evaluation study in the UK and will need to be registered as such at each participating site. In this setting, no formal informed consent is required, as data fields relate to those routinely collected as a part of standard clinical care. All participating centres will confirm that they have undergone all necessary local governance procedures prior to starting local data collection. Ethical approval processes and regulations vary between countries and obtaining informed consent from participants may be needed in some settings. We have prepared patient information sheets and consent forms for participating sites requiring these, in accordance with local regulatory processes. We expect that many participating sites will have access to waived consent procedures for the type of data collected in this study, which has been the case for large observational studies with similar methodologies.^19 30^ All data will be anonymised before it is accessed by the central study team. The study has been registered to ClinicalTrials.gov (NCT06731751) and will be reported using the Strengthening the Reporting of Observational Studies in Epidemiology statement guidelines and checklists.^31^ The study website www.plotich.org can also be accessed for all study documentations.

A full report of the study will be produced and published in an open access peer-reviewed journal with global readership. We expect many collaborators in this study; a collaborative authorship model will be used for all publications derived from the study itself, as outlined in the Guidelines for Standardising Reporting of Authorship in Collaborative Research.^32^

Results will also be communicated through presentation at relevant conferences and meetings, including existing international collaborator network and societies. Each participating site will also have access to their local data for presentation at institutional level. Lay-facing summaries of the results will be produced and shared with relevant stakeholders, communities and patient groups.
